#### Body weight

Body weight will be measured prior to the CPET at both baseline and follow-up. The same equipment will be used to measure weight of the participants at pre and post-test. Participants will be weighed without shoes, wearing exercise clothes.

#### Blood pressure

The assessor of the primary outcome (blinded for group allocation) will also measure blood pressure prior to the CPET. Measurement will be done manually, preferably on the left arm. Participants will be sitting on a chair relaxing for 3–5 min before measurements will be done. Three measurements will be performed, of which the lowest measured value will be used.

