### Outcomes

The primary outcome measure will be change in VO_2peak_. Secondary outcome measures will include exercise performance, QoL, health status, health literacy, self-perceived goal achievement, exercise habits, body weight, blood pressure, lipids and triglycerides.

All assessments will be performed at baseline and at 12 months. Outcome measures will be conducted at the same CR center as the participants were attending CR. At baseline, when the participants complete their CR, demographic data, including individual goals for the next year, will be collected. The assessments will be administrated in a standardized way, which means that all assessments for each participant will be carried out in the same order.

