### Statistical procedures

The results of the study will be reported in accordance to CONSORT statement [27]. Statistical analysis will be performed using SPSS or a similar statistical package. Descriptive data will be reported for variables of interest and will be reported as mean (standard deviation), median (range) or numbers (percent) as appropriate. The data will be analyzed following the intention-to-treat principle. Prospective differences in primary and secondary outcomes and baseline characteristics between the intervention group and the control group will be assessed by t-tests for continuous and normally distributed variables and with non-parametric tests for categorical variables. To control for confounding of between group differences, multiple linear regression modelling will be used. We expect few or none missing data in baseline characteristics. However, due to possible dropouts or participants unable to complete some of the outcome measurements, there might be missing data for both primary and secondary outcome measures at follow-up. Missing data will be assessed and analyzed with appropriate methods. All tests will be two-sided. A plan for statistical analysis will be performed in advance of each paper from the study.

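### Blood pressure is defined as the lowest of three readings: reported levels will be too low on average and precision is modestly worse than with a mean, though the shift largely cancels between arms

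*Protocol article*

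**What the plan says.** The Outcomes section of the Protocol article names blood pressure as one of the secondary outcomes: "Secondary outcome measures will include exercise performance, QoL, health status, health literacy, self-perceived goal achievement, exercise habits, body weight, blood pressure, lipids and triglycerides". On timing it says "All assessments will be performed at baseline and at 12 months".

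The Blood pressure section describes the measurement. On who takes it, the section says "The assessor of the primary outcome (blinded for group allocation) will also measure blood pressure prior to the CPET". Readings are by hand, with the left arm as the first choice. On rest beforehand, the text is "Participants will be sitting on a chair relaxing for 3–5 min before measurements will be done". It then states the derivation rule: "Three measurements will be performed, of which the lowest measured value will be used".

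Under Statistical procedures, group differences in primary and secondary outcomes "will be assessed by t-tests for continuous and normally distributed variables", with multiple linear regression for adjustment.

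The article gives no reason for taking the minimum, no within-visit SD, and no other passage that alters the rule. It does not say whether systolic and diastolic minima are taken separately or from the same reading.

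**The concern.** The rule takes three readings and throws two away, and the one it keeps is chosen because it is extreme. This has two consequences.

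- **Level.** The minimum can never exceed the mean of the same three readings. On average it sits below the person's level by an amount proportional to how much that person's readings scatter. Any blood pressure level reported, including in the baseline table, carries that shift.
- **Noise.** Under a normal model the minimum varies more from visit to visit than the mean of the same readings. The group comparison of a named secondary outcome therefore gives up some precision, although the data for a better summary are already being collected.

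Because the article states the rule outright, this is not a detail left to a later analysis plan.

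**Working it through.** **The plan's own figure.** There is none for blood pressure. The only sample-size calculation concerns peak oxygen uptake and has no bearing here.

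**Inputs from the article.** Three readings per visit; the minimum is used; same rule at baseline and 12 months; two randomised arms; blinded assessor.

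**Assumed inputs (not in the article).** Within-visit SD of a single reading, s = 3 to 8 mmHg. Between-person SD, b = 12 to 18 mmHg. For change scores, b = 15 mmHg and correlation 0.7 between the true levels at the two visits.

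**Step 1. Minimum against mean, in units of s.** The minimum of three independent normal readings has density 3φ(x)[1 − Φ(x)]². Numerical integration gives:

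| Summary | Expected error | Error variance | Error SD |
|---|---|---|---|
| Lowest of 3 | −0.846s | 0.559s² | 0.748s |
| Mean of 3 | 0 | 0.333s² | 0.577s |

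The variance ratio is 0.5595 / 0.3333 = 1.68, and the SD ratio is √1.68 = 1.30.

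**Step 2. Shift in mmHg.** 0.846 × s:
- s = 3: 2.5 mmHg
- s = 5: 4.2 mmHg
- s = 8: 6.8 mmHg

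**Step 3. Effect on a single-visit group comparison.** Ratio of total variances = (b² + 0.559s²) / (b² + 0.333s²).
- Smallest case, s = 3, b = 18: (324 + 5.04) / (324 + 3.00) = 1.006
- Middle case, s = 5, b = 15: (225 + 13.99) / (225 + 8.33) = 1.024
- Largest case, s = 8, b = 12: (144 + 35.81) / (144 + 21.33) = 1.088

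Total variance, and so the N needed for given power, rises by 0.6% to 8.8%. The standard error rises by √1.006 to √1.088, about 0.3% to 4.3%.

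**Step 4. Effect on change scores.** Ratio = [2b²(1 − 0.7) + 2 × 0.559s²] / [2b²(1 − 0.7) + 2 × 0.333s²], with 2 × 225 × 0.3 = 135.
- s = 3: 145.1 / 141.0 = 1.03
- s = 8: 206.6 / 177.7 = 1.16

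**Step 5. When the shift does not cancel.** If within-visit SD differs between arms or visits, the residual is 0.846 × the difference in SD. For 5 against 6 mmHg that is 0.85 mmHg; for 4 against 6 mmHg, 1.69 mmHg.

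**Step 6. Sensitivity to the model.** These checks were run by simulation.
- *Readings that fall in equal steps by 2 to 6 mmHg from first to third.* The minimum lies 0.7 to 5.8 mmHg below the settled (third-reading) level, the plain mean lies 1 to 3 mmHg above it, and the variance ratio is 1.69 to 2.16.
- *Right-skewed (log-normal) readings.* The variance ratio is still 1.13 at skewness 0.62 but 0.91 at skewness 0.95. The minimum becomes the less variable summary only with strong right skew.

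**The case against.** **The shift cancels in what the trial estimates.** This largely stands. The aim is a between-group effect. Allocation is randomised and stratified by rehabilitation program, each participant is assessed at the same center both times, and the blood pressure assessor is blinded. A common downward shift drops out of the group difference and of change scores. A reader might infer that the rule biases the estimated treatment effect. The article does not support that: it would require within-visit variability to differ by arm or visit, and nothing in the article suggests it does.

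**The 68% figure sounds worse than it is.** This also stands. It describes only the within-visit component. Person-to-person variation dominates, so it should not be read as a 68% loss of efficiency.

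**Not every value is too low.** Against the mean of the same three readings, the minimum is never higher. Against the person's true level the bias is in expectation only: under independent normal errors the chance that all three readings exceed it is 0.5³ = 0.125, so about 1 minimum in 8 is still too high.

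**The minimum may offset raised early readings.** This stands in part. Manual readings after a short rest, just before a maximal exercise test, may well start high, and a plain mean would then be too high. With a large fall and little scatter (6 mmHg, s = 3) the minimum is in fact nearer the settled level than the plain mean (−0.7 against +3.0 mmHg). It remains noisier, however, and the article does not offer this as its reason. Averaging the second and third readings addresses the same problem directly. With a fall in equal steps its bias is a quarter of the total fall (0.5 to 1.5 mmHg for 2 to 6 mmHg). Its error variance is 0.5s², still below 0.559s².

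**Systolic and diastolic.** A reader might infer that the two minima will come from different readings. The wording leaves that open, and a condensed article may leave it to the full protocol, so it is not counted as an error here.

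**Conclusion.** The point holds as one about measurement quality for a secondary outcome. The stated rule understates reported blood pressure by about 0.85 within-visit SDs in expectation (2.5 to 6.8 mmHg for an assumed s of 3 to 8 mmHg). It makes total variance about 1% to 9% larger than the mean would for assumed between-person SDs of 12 to 18 mmHg, or 3% to 16% larger for change scores under the single set of assumptions above. These figures rest on independent, roughly normal readings; every mmHg value is an assumption shown as a range, because the article gives no blood pressure variability.

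No material bias in the between-group comparison is shown. The primary outcome and the sample size are unaffected. The case for changing the rule is that a better summary of the same readings is available at almost no cost.

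**What to change.** Replace the last sentence of the Blood pressure section with a rule along these lines: all three readings are recorded; the outcome is their mean, calculated separately for systolic and diastolic pressure; the same rule applies at baseline and at 12 months. If the team expects early readings to be raised, specify the mean of the second and third instead. Choose one of the two before any comparison by arm. The second option gives up some of the precision gain (0.5s² against 0.333s²) in return for less upward bias.

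The cost is a wording change and keeping readings already taken. There is one small downside. If some baseline values were stored only as the minimum, the other two readings cannot be recovered. For those participants keep the minimum at both visits, and use the mean wherever all readings exist. Record which rule applied to whom; it is settled by the baseline record and so cannot depend on follow-up results.

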#### Blood samples

Blood samples including LDL cholesterol, HDL cholesterol, total cholesterol and triglycerides will be evaluated. Participants will be encouraged to take fasting blood samples at their general practitioner at inclusion to the study and at follow-up. They are asked to bring the results to baseline and the 12 months assessment.

### Statistical procedures

The results of the study will be reported in accordance to CONSORT statement [27]. Statistical analysis will be performed using SPSS or a similar statistical package. Descriptive data will be reported for variables of interest and will be reported as mean (standard deviation), median (range) or numbers (percent) as appropriate. The data will be analyzed following the intention-to-treat principle. Prospective differences in primary and secondary outcomes and baseline characteristics between the intervention group and the control group will be assessed by t-tests for continuous and normally distributed variables and with non-parametric tests for categorical variables. To control for confounding of between group differences, multiple linear regression modelling will be used. We expect few or none missing data in baseline characteristics. However, due to possible dropouts or participants unable to complete some of the outcome measurements, there might be missing data for both primary and secondary outcome measures at follow-up. Missing data will be assessed and analyzed with appropriate methods. All tests will be two-sided. A plan for statistical analysis will be performed in advance of each paper from the study.

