### Randomization

Participants will be randomly assigned at a 1:1 ratio in variable blocks to the intervention group and the control group. The randomization will be stratified to ensure equal numbers of participants from the three different CR programs in the intervention- and control group, respectively. A computer-generated, permuted block randomization scheme will be used to allocate the participants. To minimize bias, and to optimize the rigor of the RCT, a number of methodological factors have been incorporated into the design of the study. Participants will be randomly allocated to the groups via concealed allocation. Due to the nature of the intervention, it is impossible to blind the participants, nor the supervisor giving the follow-up, to the allocated groups. However, assessors for primary outcome measure will be blinded to the allocated groups. Further, intention-to-treat analyzes will be conducted to reduce bias. This maintains the random assignment to the groups and imitate the real-life situation.

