#### Peak oxygen uptake

The participants will perform a CPET before entering the study to ensure eligibility and to measure VO_2peak._ Relative VO_2peak_ (ml/kg/min) will be the primary outcome. VO_2peak_ will be conducted and analyzed using Vyntus CPX (Vyaire Medical, Höchberg, Germany) at one of the CR centers. At the other center, Schiller Ganshorn Ergo Spirometry (Schiller AB, Baar, Switzerland) will be used. Two standardized protocols are drafted on a treadmill. The walking protocol starts at 3.5 km/h and 0% incline for 2 min, followed by increased velocity by 0.5 km/h and inclination by 1% per minute. When 6 km/h is reached, only incline increase each minute with 2%. The running-protocol starts at 5 km/h and 0% inclination for 2 min, followed by increased velocity by 1 km/h and 2% inclination respectively every other minute. The same treadmill protocol will be used at baseline and follow-up.

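### The primary group comparison rests on an unadjusted t-test and an unranked regression; neither baseline VO2peak nor the randomisation stratum is a pre-named covariate

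*Protocol article*

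**What the plan says.** Statistical procedures names the test for primary and secondary outcomes: differences between the groups "will be assessed by t-tests for continuous and normally distributed variables and with non-parametric tests for categorical variables". The same sentence covers baseline characteristics. The next one reads: "To control for confounding of between group differences, multiple linear regression modelling will be used". No covariates are listed, and the two analyses are not ranked. The section also promises an analysis plan ahead of each paper.

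Randomization states: "The randomization will be stratified to ensure equal numbers of participants from the three different CR programs in the intervention- and control group, respectively". The analysis text does not mention this factor again.

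Outcomes states: "The primary outcome measure will be change in VO_2peak". Peak oxygen uptake instead calls relative VO2peak in ml/kg/min the primary outcome, without mentioning change.

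Sample size takes a difference of 3.5 ml/kg/min, an SD of 6 ml/kg/min, 80% power and α = 0.05, and arrives at 47 per group. It then sets a total of 113 to allow for 20% dropout. It does not say whether 6 is the SD of VO2peak values or of change.

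**The concern.** Two things are badly fixed.

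First, the reader cannot tell which estimate is the trial's answer. A t-test and a regression with unnamed covariates can give different estimates and intervals. The reason given for the regression does not help. Randomisation already removes systematic confounding; adjustment in a trial serves precision and respects the stratified design. Tying it to confounding, next to tests of baseline characteristics, leaves room to choose covariates after imbalances have been seen.

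Second, the test that is named gives up precision that the data could supply. Baseline VO2peak is measured before entry and is probably a strong predictor of the 12-month value. A change score fixes its slope at 1, whereas ANCOVA estimates it. The design also balances the arms within three programmes, but the t-test leaves any programme differences in the outcome in its error term. What is at stake is the width of the primary confidence interval and some power.

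**Working it through.** **Inputs from the protocol article.** Difference 3.5, SD 6, two-sided α 0.05, 47 per group, total 113, 20% dropout; three programmes of about one third each; 1:1 allocation within programme.

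**Assumed, not in the documents.** Correlation r between baseline and 12-month VO2peak of 0.5 to 0.9, with equal SDs at both times; share R² of outcome variance explained by programme of 0 to 0.3.

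**1. The plan's own figure.** n per group = 2 × (1.960 + 0.842)² × 6² / 3.5² = 46.1, rounded up to 47. Exact t-test power at 47 per group is 79.9%. So 47 reproduces for an unadjusted two-sample comparison.

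**2. Completers.** 113 × 0.8 = 90.4, or about 45 per group. Exact t-test power there, at SD 6, is 78.1%.

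**3. Baseline adjustment if 6 is the SD of change.** With σ the SD of VO2peak values, the variance of change is 2σ²(1−r) and the ANCOVA residual variance is σ²(1−r²). The ratio is (1+r)/2, so the ANCOVA SD is 6 × √((1+r)/2).

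| r (assumed) | Variance ratio | ANCOVA SD | Power at 45 per group |
|---|---|---|---|
| t-test on change | 1 | 6.00 | 78% |
| 0.5 | 0.75 | 5.20 | 88% |
| 0.7 | 0.85 | 5.53 | 84% |
| 0.9 | 0.95 | 5.85 | 80% |

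Removing three further degrees of freedom leaves these percentages unchanged to the nearest whole number.

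**4. If 6 is the SD of VO2peak values.** The change SD is 6 × √(2(1−r)) and the ANCOVA SD is 6 × √(1−r²). At r = 0.5 these are 6.00 and 5.20, giving power of 78% against 88%. At r = 0.7 they are 4.65 and 4.28, giving 94% against 97%. At r = 0.9 both exceed 99%. A t-test on 12-month values alone would stay at 78% throughout.

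**5. Strata.** With exact balance within programme, the t-test's standard error is too large by a factor of about 1/√(1−R²). A simulation (20,000 runs per setting, three equal strata, 45 per arm, total SD 6) gave:

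| R² (assumed) | Mean t-test SE / true SE | Type I error, t-test | Type I error, with strata | Power, t-test | Power, with strata |
|---|---|---|---|---|---|
| 0 | 1.00 | 4.8% | 4.8% | 78% | 78% |
| 0.1 | 1.06 | 3.9% | 5.0% | 79% | 82% |
| 0.2 | 1.12 | 2.8% | 5.1% | 81% | 87% |
| 0.3 | 1.20 | 1.8% | 4.8% | 82% | 90% |

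Here R² refers to whichever outcome is analysed. For a change score it is the share of variance in *change* that programme explains.

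**The case against.** The strongest reply is that the protocol already names multiple linear regression, which is the right class of model, and that covariates are normally left to the analysis plan promised for each paper. This stands in part: an adjusted analysis is not absent, and a missing covariate list alone would be no finding. But the article does commit to a specific test for the primary outcome, leaves the regression unranked, and gives it a rationale that points to confounders rather than to baseline and stratum. A later plan would have to change that commitment, not just fill it in.

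Four stronger readings are tempting, and the documents do not support them.

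- *Baseline is ignored.* Not for the outcome as defined under Outcomes: change uses baseline by subtraction. The larger gain over a 12-month-only t-test would apply only if the wording under Peak oxygen uptake, which omits change, governed the analysis.
- *Device differences inflate the error.* The centres use different CPET systems ("At the other center, Schiller Ganshorn Ergo Spirometry (Schiller AB, Baar, Switzerland) will be used"), but each participant is assessed at the same centre both times and on the same treadmill protocol. Additive centre or device differences in level therefore largely cancel in a change score. Only programme differences in mean change would remain.
- *The standard errors invalidate the test.* Any error runs in the conservative direction, with no excess of false positives, and it vanishes if programme does not predict the outcome.
- *Dropouts are simply discarded.* Statistical procedures promises suitable methods for missing data, and the Discussion names linear mixed models, multiple imputation and sensitivity analysis.

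It is also fair to say that the 78% starting point is not the t-test's fault. It comes from having about 45 rather than 47 completers per group.

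**Conclusion.** The point holds as one of efficiency and clarity, not validity. The primary analysis is not singled out, and the named test is less precise than a model on baseline and stratum would be. On the declared change outcome, and if 6 is the SD of change, the gain from baseline adjustment is modest: from 78% to between 80% and 88% power over the assumed range of r. Any gain from the strata depends on how far programme predicts change, which may be little. Neither r nor R² is given in the documents, so the sizes are conditional. The direction is not: over the assumed ranges, adjustment improves precision or leaves it essentially unchanged. The change should be made, but the trial's conclusions would not be unsound without it.

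**What to change.** Name a single primary analysis: a linear model of 12-month VO2peak on group, baseline VO2peak and CR programme (three levels), reporting the adjusted mean difference with its 95% CI. This remains compatible with a change outcome, because regressing change on the same terms gives the same group estimate; only the baseline coefficient shifts by 1. An equivalent choice, in line with the methods listed in the Discussion, is a mixed model of both time points with a common baseline mean and programme terms, which keeps participants who have only a baseline value.

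Use the same form for continuous secondary outcomes measured at baseline. Keep the t-test as a supportive display, and replace the confounding rationale with the pre-named covariates.

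The cost is about one sentence and three degrees of freedom (one for baseline, two for programme). No new data are needed.

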### Sample size

The sample size has been estimated from the primary outcome, peak oxygen consumption (VO_2peak_). A difference of 3.5 ml/kg/min in VO_2peak_ is regarded to be clinically relevant due to respectively 12–13 and 17% improvements in survival in men and women, with and without coronary heart disease [28–31]. The associated standard deviation was estimated to be 6 ml/kg/min based on the feasibility study conducted in the population [13]. This implies a moderate effect size (0.58). Given a power of 80% and level α = 0.05, a sample size of 47 in each group will be sufficient to detect a clinically relevant difference between groups. To allow for a 20% dropout, we aim at including 113 participants.

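### The article tests baseline differences between randomised groups and gives the primary outcome both a t-test and a regression against confounding, with the analysis plan timed to papers rather than to data access

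*Protocol article*

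**What the plan says.** Four statements in the protocol article bear on this point.

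- **Tests.** Statistical procedures: "Prospective differences in primary and secondary outcomes and baseline characteristics between the intervention group and the control group will be assessed by t-tests" (non-parametric tests are given for categorical variables). Outcomes and baseline characteristics stand in the same list of tested variables.
- **Adjustment.** The next sentence: "To control for confounding of between group differences, multiple linear regression modelling will be used".
- **Timing.** The section closes: "A plan for statistical analysis will be performed in advance of each paper from the study".
- **Design and outcome.** Randomization: "Participants will be randomly assigned at a 1:1 ratio in variable blocks", with concealed allocation, and "The randomization will be stratified to ensure equal numbers of participants from the three different CR programs". Outcomes: "The primary outcome measure will be change in VO_2peak".

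**The concern.** Under concealed random allocation, every baseline difference between the arms is due to chance. A test of that difference examines a null hypothesis already known to be true. A significant result is no evidence of a fault, and a non-significant one gives no assurance that a prognostic imbalance is harmless.

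Confounding is a reason to adjust in an observational study. In this trial the sound reasons are precision, since baseline VO2peak predicts VO2peak at 12 months, and respect for the stratified design, since CR programme was used in the allocation. The article's stated reason points to neither.

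The article also sends the primary outcome through a t-test and through a regression without ranking them. If the two disagree, nothing in the text settles which result is the trial's answer. A plan fixed before group results are seen would close that gap. The timing rule does not require this, because it is anchored to papers. All outcomes are measured at the same two visits, so a plan for a second paper could satisfy the rule after group results are known.

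**Working it through.** **Step 1. The plan's own figure.** Inputs from Sample size: difference 3.5, SD 6 ml/kg/min, "Given a power of 80% and level α = 0.05, a sample size of 47 in each group will be sufficient"; from Statistical procedures: "All tests will be two-sided".

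n per group = 2 × (1.960 + 0.842)² × 6² / 3.5² = 46.1, so 47. The t-based solution is 47.1. Power at 47 per group is 80.7% (normal) or 79.9% (t). The figure reproduces. It is an unadjusted two-group calculation, so this point does not disturb it.

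**Step 2. What the baseline tests would show.** With sound randomisation and k independent characteristics, P(at least one p < 0.05) = 1 − 0.95^k. This gives 22.6% for k = 5, 40.1% for k = 10 and 64.2% for k = 20. The article does not give k, so these values are assumptions.

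**Step 3. Power for the stated outcome.** Assumptions not in the article: baseline-to-12-month correlation r of 0.6 to 0.8; the SD of 6 applies to VO2peak at each visit; normal data; no missing values; strata ignored.

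- SD of change = 6 × √(2(1 − r))
- Residual SD under ANCOVA = 6 × √(1 − r²)
- Non-centrality = (3.5 / SD) × √(47/2); power from the non-central t at two-sided 0.05

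| r | SD change | Power, t-test on change | SD ANCOVA | Power, ANCOVA | Gain (points) |
|---|---|---|---|---|---|
| 0.6 | 5.37 | 87.9% | 4.80 | 93.8% | 5.9 |
| 0.7 | 4.65 | 95.1% | 4.28 | 97.5% | 2.4 |
| 0.8 | 3.79 | 99.3% | 3.60 | 99.7% | 0.4 |

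The article does not say whether 6 is the SD at one visit or the SD of change. If it is the SD of change, the t-test on change has 79.9% power. The ANCOVA residual SD is then 6 × √((1 + r)/2) = 5.37, 5.53 and 5.69, which gives 87.9%, 85.9% and 83.9%. The gain is then 8, 6 and 4 points.

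**Step 4. Type I error with two candidate analyses.** Simulation under the null, 47 per arm, 40,000 runs at each of r = 0.6, 0.7 and 0.8:

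- t-test on change alone: 5.0, 5.0, 4.9%
- fixed ANCOVA alone: 4.9, 4.9, 5.0%
- the more favourable of the two: 7.0, 6.8, 6.4%
- t-test on change, replaced by ANCOVA only if the baseline VO2peak test has p < 0.05: 4.5, 4.6, 4.7%

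The inflation comes from free choice between analyses. A mechanical pre-test rule does not inflate the error.

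**The case against.** The best defence is that most of the harm would have to come from things the article does not say.

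- **Covariate selection.** A reader might infer from the adjacent sentences that the baseline tests will choose the regression covariates. The text does not say so, and baseline VO2peak and CR programme could equally be fixed covariates. Covariate selection is therefore a risk and not a stated procedure. Even if it were followed for baseline VO2peak, Step 4 shows close to nominal type I error on the change score.
- **Missing covariate list.** A journal article may leave the list of covariates to the analysis plan. That omission is no finding, and this point does not rest on it.
- **Timing.** A plan written before each paper may still precede access to the data, and the primary outcome would normally be in the first paper. A reader might infer that the primary estimate will be chosen after results are seen; the wording permits this but does not show it.
- **Size.** A reader might measure the power loss against a t-test on VO2peak at 12 months alone and find it large. The Outcomes section makes change the primary outcome, so that comparison does not apply. The Peak oxygen uptake section's reference to relative VO2peak is naturally read as fixing the unit.

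All four stand as limits on the point. They do not answer what the article does state: tests of baseline characteristics after randomisation, confounding as the reason for adjustment, two unranked analyses of one primary outcome, and a plan anchored to papers.

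**Conclusion.** The point holds in limited form. The baseline tests are uninformative, the rationale for regression is wrong for a randomised trial, and the article leaves two analyses open for the primary outcome under a timing rule that does not by itself exclude a choice after the data are seen.

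The cost is modest. For change in VO2peak with 47 per arm, fixing ANCOVA in advance gains about 6 points of power at r = 0.6 and under 1 point at r = 0.8 if 6 is the SD at each visit, or about 8 to 4 points if it is the SD of change. Reporting whichever of the two analyses is more favourable would raise type I error to about 7%. That is the worst case of free choice between these two and says nothing about what the investigators intend. The correlation range is assumed throughout. The documents do not support a claim that the primary inference is already data-dependent, or that most of the precision available from adjustment is lost. The trial's validity is not in question.

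**What to change.** Three changes to Statistical procedures:

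1. Remove baseline characteristics from the list of tested variables and report them by group descriptively only.
2. For the primary outcome, replace the t-test and the confounding sentence with one linear model of VO2peak at 12 months (or of change), adjusted for baseline VO2peak and CR programme. Name it as the sole basis for the primary conclusion and label all other analyses of that outcome as sensitivity analyses.
3. Reword the closing sentence so that the plan for the primary and all listed secondary outcomes is final before any 12-month data are examined by group.

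The cost is one deleted clause and two reworded sentences. Baseline VO2peak and CR programme are already recorded, so no further data, participants or visits are needed, and the 47 per group stands.
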